## Abstract

**Background:**

Alcoholic hepatitis is the most florid presentation of alcohol-related liver disease. In its severe form, defined by a Maddrey’s discriminant function (DF) ≥32, the 28-day mortality rate is approximately 35%. A number of potential treatments have been subjected to clinical trials, of which two, corticosteroids and pentoxifylline, may have therapeutic benefit. The role of corticosteroids is controversial as trial results have been inconsistent, whereas the role of pentoxifylline requires confirmation as only one previous placebo-controlled trial has been published.

**Methods/design:**

STOPAH is a multicentre, double-blind, factorial (2 × 2) trial in which patients are randomised to one of four groups:

1. Group A: placebo / placebo

2. Group B: placebo / prednisolone

3. Group C: pentoxifylline / placebo

4. Group D: pentoxifylline / prednisolone

The trial aims to randomise 1,200 patients with severe alcoholic hepatitis, in order to provide sufficient power to determine whether either of the two interventions is effective. The primary endpoint of the study is mortality at 28 days, with secondary endpoints being mortality at 90 days and 1 year.

**Discussion:**

STOPAH aims to be a definitive study to resolve controversy around the existing treatments for alcoholic hepatitis. Eligibility criteria are based on clinical parameters rather than liver biopsy, which are aligned with standard clinical practice in most hospitals. The use of a factorial design will allow two treatments to be evaluated in parallel, with efficient use of patient numbers to achieve high statistical power.

**Trial registration:**

EudraCT reference number: 2009-013897-42

ISRCTN reference number: ISRCTN88782125

## Background

Alcohol-related illness places an enormous burden upon health services. A recent review of the burden of liver disease in Europe confirms the prominence of alcohol as the most important cause of cirrhosis and liver-related mortality in Europe. In the UK it has been estimated by the Royal College of Physicians of London that the inpatient costs in 1998-1999 arising from the consequences of alcohol misuse were as high as £2.9 billion [1]. Overall, alcohol-related deaths in the UK have more than doubled since 1979, and in Scotland have increased by 236% between 1980 and 2002 [2,3]. Throughout the UK deaths from cirrhosis have risen dramatically between 1987 and 1991 [4]. Alcohol-related liver disease (ALD) accounts for majority of alcohol-related deaths in the UK [5]. While many patients presenting with alcoholic liver disease will have cirrhosis, as many as 60% will have evidence of an alcohol-related hepatitis [6]. Alcoholic hepatitis is the most florid manifestation of alcohol-related liver disease, but is potentially reversible. However the short-term mortality of alcoholic hepatitis is particularly high among those with indicators of severe disease. The 28-day mortality of patients who have a Maddrey’s discriminant function (DF) ≥32 is 30% to 40% [7-9]. The 28-day mortality of patients who have a Glasgow Alcoholic Hepatitis Score (GAHS) ≥9 is approximately 60% [10]. Alcoholic hepatitis affects a relatively young population (average age, 50 years; patients may present in their 20s and 30s). Despite the increasing prevalence and the severity of this disease, there is no consistency in its management.

Since 1971 there have been 13 randomised studies and four meta-analyses investigating the role of corticosteroid therapy for alcoholic hepatitis [11]. Despite this apparent wealth of evidence, controversy persists. There remains deep division with regard to the use of corticosteroids. Advocates of the treatment cite significant improvement in the short to medium term mortality, while detractors cite the risks of sepsis and gastrointestinal haemorrhage with corticosteroid therapy. Many of the published studies have been plagued by widely varying inclusion and exclusion criteria. The largest placebo-controlled study treated 90 patients and found no benefit with prednisolone compared with a similar placebo-treated group [12]. This study was hampered by the inclusion of patients with both moderate and severe alcoholic hepatitis, as well as end-stage alcoholic liver disease. In the only study to require histological confirmation of alcoholic hepatitis in all patients, prednisolone was associated with a short-term improvement in mortality in patients, although this benefit was not apparent after 2 years [13,14]. However, on review of the published studies, none of these reach an adequate statistical power to make a statement with 80% confidence. The most recent meta-analysis by the Cochrane Group, of all of the available trials, demonstrated that although there was a trend of benefit with corticosteroids, the results were not statistically significant (*P*=0.2) [15]. However, a re-analysis of the five most recent studies indicated a significant benefit from corticosteroid [16]. In this study, patients with DF ≥32 treated with prednisolone had a 28-day mortality of 20%, as opposed to a mortality of 34.3% among placebo-treated patients (*P*=0.006).

Pentoxifylline has also recently been studied in the treatment of alcoholic hepatitis. It is believed to act, in part, by inhibiting the synthesis of the pro-inflammatory cytokine tumour necrosis factor alpha. There has been one randomised placebo controlled trial which showed significant benefit [17]. One hundred patients were enrolled, all with a DF >32. Pentoxifylline was administered for 4 weeks, at a dose of 400 mg TDS. A total of 12/49 (24.5%) in the pentoxifylline group died compared to 24/52 (46.1%) in the placebo group during the index hospitalisation (*P*=0.037). The principal benefit for the agent appeared to be a reduction of deaths attributed to hepatorenal syndrome.

One study has compared prednisolone with pentoxifylline and suggested a survival benefit with pentoxifylline at 3 months (85.3% compared to 64.7%; *P*=0.04). Hepatorenal failure again appeared to be less in the pentoxifylline group. However, this was a small study with only 34 patients in each group [18]. The comparison of prednisolone alone against prednisolone plus pentoxifylline has been assessed in two studies. The COPE Trial studied 70 patients and found similar 28-day survival for steroid treated patients with or without pentoxifylline (73.5% and 72.2%, respectively) [19]. A further study published in abstract form was similarly unable to show a difference in the rate of 28-day mortality [20]. In addition, one study looked at the effect of switching from prednisolone to pentoxifylline in those patients who showed no evidence of a response after 7 days of steroid treatment [21]. Again there was no difference in mortality between these groups.

The primary objective of this study is to determine whether corticosteroids or pentoxifylline reduce the mortality associated with severe alcoholic hepatitis at 28 days, 90 days and 1 year. In order to avoid the controversies caused by underpowered studies in this field, we aim to conduct a well-powered definitive study.

## Methods/design

The study design is a multicentre, double-blind, factorial (2 × 2) trial in which patients are randomised to one of four groups:

1 Group A: placebo / placebo

2 Group B: placebo / prednisolone

3 Group C: pentoxifylline / placebo

4 Group D: pentoxifylline / prednisolone

Patients admitted to participating hospitals with a clinical diagnosis of alcoholic hepatitis are screened using the inclusion and exclusion criteria below. Clinical and demographic data are transmitted to the TENALEA web-based registration/randomisation service, which randomises the patient to a treatment group stratified by disease severity and geographical region.

### Clinical study endpoints

The primary endpoint is mortality at 28 days; this time point represents the end of the peak period of mortality for alcoholic hepatitis and is consistent with other trials in the field [22]. Secondary endpoints will look at mortality at 90 days and 1 year, outcome relative to GAHS, rates of recidivism, hospital re-admission rates for liver or non-liver related events, rates of gastrointestinal haemorrhage and sepsis, and rates of new or recurrent renal failure (serum creatinine >500 μmol/L or requiring renal support) and any other adverse events or serious adverse events recorded using NCI CTCAE v4.0). In addition incremental NHS costs and quality of life (QOL) using SF36 and EQ-5D will be collected to facilitate health economic analysis.

### Patient population

Patients, at least 18 years of age, with a clinical diagnosis of alcoholic hepatitis on admission to hospital are considered for inclusion in the study. Eligibility criteria (Appendices A & B) are used to select those patients with severe alcoholic hepatitis (defined by a Maddrey’s DF >32) and to exclude patients with other hepatological diagnoses. As the trial is being conducted in more than 60 hospitals across the UK, many of which do not have access to transjugular liver biopsy, it was decided not to make liver histology an entry criteria. However, in order to exclude patients with decompensated cirrhosis, a strict time limit was set on the duration of jaundice.

In the majority of published trials, patients with gastrointestinal bleeding, sepsis and renal failure prior to randomisation have been excluded from the study. In this trial, patients with gastrointestinal bleeding are eligible for randomisation once they have been stabilised for 48 h. All patients are carefully screened for infection, by clinical examination, chest radiology, blood and urine cultures and, if found to have evidence of sepsis, are treated with appropriate antibiotics for a minimum of 2 days. Once the local investigator considers the infection to be under control, the patient is then eligible for randomisation. This strategy is justified by the recent observation that the outlook of patients with AH receiving corticosteroids is unaffected by their having had a recent infection treated with antibiotics [23]. Patients who are oligo-anuric (urine output < 400 mL / 24 h), have a creatinine >500 uM/L or who require renal support, are given appropriate resuscitation therapy for up to 1 week. These patients may then be re-screened and considered for randomisation, once they meet eligibility criteria.

### Consent

Patient information sheets are given to potential patients at least 24 h before consent is sought. Potential patients for the trial who present with hepatic encephalopathy may be unable to consent for themselves, but are not excluded from the trial. Special arrangements are in place to ensure that the interests of such patients are protected. When considering a patient who is unable to consent for themselves for suitability for the trial, the decision on whether to consent to, or refuse, participation in a trial is taken by a ‘legal representative’ who is independent of the research team and who acts on the basis of the person’s presumed wishes. The legal representative is generally the next of kin but where the next of kin is not available or unwilling to take the decision, a hospital-appointed medical practitioner unconnected to the trial is asked to provide consent. The consent given by the legal representative remains valid in law until such time as the patient recovers capacity. At this point, the patient is informed about the trial and asked to decide whether or not they want to continue in the trial, and consent to continue is sought from the patient themself.

### Randomisation

After consent is given, patients are registered in the trial via TENALEA, a web-based registration and randomisation system, and then undergo screening assessments. If eligible for the study, patients are randomised via the ALEA system to a study treatment group, which is blinded to the site staff and the patient, by means of a unique four-digit patient pack number.

Randomisation is block stratified and performed using the following two stratification factors:

1. Geographic region (12 in total)

2. Risk group: either high or intermediate risk (high risk is defined as either sepsis or history of GI bleeding in the previous 7 days or creatinine >150 μmol/L or any combination of the these; intermediate risk is defined as no sepsis and no history of GI bleeding in the previous 7 days and creatinine ≤150 μmol/L).

### Intervention

Each patient is provided with two bottles labeled ‘Bottle A’ and ‘Bottle B’ containing the investigational medical products. Bottle A contains opaque gelatin capsules filled either with tablets of pentoxifylline 400 mg or identical placebo capsules filled with microcrystalline cellulose. Patients are instructed to take one capsule from bottle A three times daily. Bottle B contains opaque gelatin capsules filled either with tablets of prednisolone 40 mg or identical placebo capsules filled with microcrystalline cellulose. Patients are instructed to take one capsule from bottle B once daily. Both medications are administered for 28 days.

Alcohol withdrawal therapy is administered if required. All patients receive supportive nutritional therapy with nutritional supplements in the first instance. If they are unable to take these, they are offered enteral nutrition via a nasogastric tube with the aim of providing 35 to 40 kcal/kg/day non-protein energy with 1.5 g/kg/day protein.

### Evaluations during and after treatment

Patients are evaluated while an inpatient on treatment days 7, 14, 21, and 28 and at each time point recordings made of vital signs, WHO performance status, concomitant medication and adverse events. Blood samples are taken for liver function tests, prothrombin time, full blood count, urea and creatinine. Patients are assessed for the presence of hepatic encephalopathy and the occurrence of GI bleed or sepsis in previous 7 days. If patients are discharged from hospital before the end of treatment, assessments are made at 28 days by telephone interview. A complete schedule of procedures is given in Additional file 1 (Trial Procedures; Schedule of procedures).

After discharge from hospital, patients are evaluated at 90 days and at one year. At each time point recordings are made of vital signs, WHO performance status, concomitant medication and adverse events. Blood samples are taken for liver function tests, prothrombin time, full blood count, urea and creatinine. Patients are assessed for the presence of hepatic encephalopathy and the occurrence of GI bleed or sepsis since previous assessment. In addition, patients are asked to complete a quality of life questionnaire (Short Form 36 and EQ-5D) and an assessment is made of their current alcohol consumption. At registration patients are asked to consent to follow-up via medical research information service, now called the NHS Information Centre Data Linkage service. This ensures that if patients are lost to follow-up should the patient die, we would obtain their date of death for analysis via this service.

### Statistical considerations

#### Power calculation

In order to estimate the required trial sample size a power calculation was performed in nQuery Advisor using a two group continuity corrected χ^2^ test and the following parameters:

• Power = 90% (to allow for secondary outcomes)

• Two-sided significance level of 5%

• Estimated 28-day mortality rate in each treatment group is given in Table 1.

**Table 1 T1:** Estimated 28 day mortality rates for power calculation

		**Pentoxifylline**		
		**Yes**	**No**	**Total**
Prednisolone	Yes	17%^a^ Group D	25% Group B	21%
	No	25% Group C	35% Group A	30%
	Total	21%	30%	

^a^Estimated assuming no interaction, that is multiplicative independent effects.

Based on a reduction in the 28-day mortality rate at the margins from 30% to 21%, a sample size of 513 per group of single agent *versus* no single agent would be required. Thus in total the trial would require 1,026 patients. We have allowed for an approximate 10% withdrawal/lost to follow-up rate and will therefore aim to recruit 1,200 patients to the study, with patients being evenly allocated to each treatment arm.

The sample size for this trial has not been powered to assess for any observed treatment interaction and in fact assumes no interaction between the two treatments (that is, that receiving prednisolone in addition to pentoxifylline does not change the effect of pentoxyfylline and *vice versa*). To be able to assess the interaction of two treatments, while keeping power at 90%, generally requires an increase in the sample size by four-fold [24]. As assessing the size of any interaction was not of primary interest as it was assumed to be small or non-existent, it was deemed appropriate to not power for assessing an interaction.

### Statistical analyses

Analysis will be on the basis of intention to treat (ITT). In order to determine the efficacy of prednisolone, the 28-day mortality rate in those treated with prednisolone (that is, Groups B and D) will be compared with the mortality rate in control groups (Groups A and C). Similarly, the efficacy of pentoxifylline will be assessed by comparing the 28-day mortality rate in Groups C and D with the mortality rate in Groups A and B.

Although the study is not powered to detect a difference between two active treatments and single agent therapy, we will make this comparison for 28-day mortality rates. Logistic regression will be used to compare 28-day mortality between the treatment groups. The impact of pre-treatment variables such as gastrointestinal bleeding, sepsis or renal impairment on admission will be estimated by adding these covariates to the logistic regression analysis. Mortality rates at 90 days and 12 months will be compared using the same strategy. All analyses will be adjusted for the stratification variables and assessed at the two-sided 5% significance level. However, the impact of recidivism and hospital re-admission will also be assessed in relation to these outcomes.

Overall mortality will also be analysed as a secondary endpoint using the method of Kaplan-Meier and a cox-proportional hazards model adjusting for the same variables as explained above.

Rates of gastrointestinal bleeding, sepsis and renal failure will be summarised over time and by arm.

Stata for Windows (StataCorp) and SAS (SAS insititute inc) will be the statistical packages of choice. The study will be reported in accordance with the CONSORT (Consolidated Standards of Reporting Trials) statement.

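### Baseline GAHS, prognostic by the protocol's own figures and already planned for use, is not named as a covariate in the efficacy models: a missed efficiency, not an error

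*Protocol article*

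**What the plan says.** Under Statistical analyses, the protocol article compares 28-day mortality by logistic regression at each factorial margin and says "All analyses will be adjusted for the stratification variables and assessed at the two-sided 5% significance level". Under Randomisation, the stratification variables are geographic region (12 levels) and "Risk group: either high or intermediate risk". High risk means sepsis, gastrointestinal bleeding in the previous 7 days, creatinine above 150 μmol/L, or any combination.

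The same Statistical analyses section adds pre-treatment variables to the logistic model so that their impact can be estimated. It gives gastrointestinal bleeding, sepsis and renal impairment as examples. Mortality at 90 days and 12 months follows the same strategy, and the Cox model uses the same variables.

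GAHS appears in two other places. The Background says that 28-day mortality at "Glasgow Alcoholic Hepatitis Score (GAHS) ≥9 is approximately 60"%, and gives 30% to 40% for DF ≥32. Clinical study endpoints lists "outcome relative to GAHS" among the secondary endpoints. GAHS is not named as a covariate anywhere.

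**The concern.** The article describes GAHS as a marker that separates patients sharply by 28-day risk, and the trial plans to use it. Yet the stated adjustment set, and every example of a further covariate, covers only the complications that define the risk group.

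In a logistic model, conditioning on a strong baseline predictor increases the power of the treatment test without any more patients. Leaving it out gives up that gain. Because the list of additional covariates is open, a borderline 28-day result could also be disputed through adjusted models chosen after the data are seen. Naming the covariate in advance deals with both problems.

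**Working it through.** **1. The plan's own sample size.** Inputs from Power calculation: "Two-sided significance level of 5"%; "Power = 90% (to allow for secondary outcomes"); a "two group continuity corrected" χ² test; and "Based on a reduction in the 28-day mortality rate at the margins from 30% to 21"%.

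- Uncorrected: n = [1.960·√(2·0.255·0.745) + 1.282·√(0.30·0.70 + 0.21·0.79)]² / 0.09² = 490.8, so 491 per margin.
- Continuity-corrected: n′ = (490.8/4)·[1 + √(1 + 4/(490.8·0.09))]² = 512.8, so 513 per margin and 1,026 in total.

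This matches the stated figure exactly. The calculation involves no covariates, so the sample size does not depend on this point. With 1,200 recruited and 10% lost, 1,080 are evaluable. Power for 30% versus 21%, without continuity correction, is then 92.5% (91.2% at 1,026).

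**2. What the GAHS figures imply.** Take Group A mortality as 35% (Table 1) and mortality at GAHS ≥9 as 60% (Background). The share q with GAHS ≥9 is not given, so it is varied as an assumption. Mortality below 9 then follows as (0.35 − 0.60q)/(1 − q).

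**3. Power with and without GAHS.** A 2×2 logistic simulation was run with 3,000 replicates per row and n = 1,080. It used a common odds ratio per drug, no interaction, and an effect set so that Groups B and C have 25% mortality. Group D then comes out at 16.5–17.1%, in line with the 17% in Table 1. GAHS enters as a binary indicator. The information gain is the squared ratio of the mean treatment z-statistics, minus 1.

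| Assumed share at GAHS ≥9 | Implied mortality below 9 | Power without GAHS | Power with GAHS | Information gain |
|---|---|---|---|---|
| 20% | 28.7% | 93.6% | 94.8% | 6.7% |
| 30% | 24.3% | 94.5% | 96.2% | 11.0% |
| 40% | 18.3% | 93.9% | 96.3% | 16.7% |
| 50% | 10.0% | 94.3% | 98.0% | 24.2% |

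The gains are 1.2, 1.7, 2.4 and 3.7 points, with simulation error of about 0.5 points on each power. Converting the first row's powers directly gives [(1.626 + 1.96)/(1.522 + 1.96)]² = 1.06. Hence the quoted range of roughly 6–24%.

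A continuous score at n = 1,026, with assumed AUC of 0.61, 0.68, 0.74 and 0.79, gives a similar picture: 91.1% to 91.9%, 92.3% to 93.5%, 92.4% to 95.9%, and 92.4% to 97.0%.

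**4. With a risk flag in both models.** The comparator in step 3 omits the planned risk group. A second simulation at n = 1,080 put a risk flag in both models. Its assumptions are flag prevalence of 40% at GAHS ≥9 and 20% below, a flag odds ratio of 1.5 or 2.5, and 29–50% of patients at ≥9. Power rises from 93–96% to 95–98%, and information by 8–23%. Region was not modelled.

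**5. A smaller true effect.** If power without GAHS were 60%, power with it would be Φ(√r·(0.253 + 1.96) − 1.96), where r is 1 plus the information gain. At r = 1.06 this is about 62%, and at r = 1.242 about 69%. With the risk flag in both models and an effect of 35% to 28.5%, simulated power rises from 62–67% to 66–74%.

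**The case against.** The strongest reply is that nothing here is wrong. Adjusting for the stratification factors matches the randomisation, the sample size rests on an unadjusted test, and planned power exceeds 90% without GAHS. All of that stands. Part of the apparent shrinkage of the odds ratio without GAHS is also non-collapsibility: the marginal and conditional odds ratios are different quantities, and the strata-adjusted test is not invalid.

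A second reply is that covariate lists belong in the statistical analysis plan, which is not shown and may name GAHS. That is possible, and then the action is a check. But the article does state an adjustment set for all analyses, so this point comments on a stated choice and not on omitted detail.

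Four stronger readings are tempting but not supported:

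- **That the models adjust for the strata alone.** The list of further covariates is open, so GAHS is not excluded. It is simply not named, and the listed terms are described as estimating impact.
- **That DF is an equally strong omitted predictor.** Every patient must have DF ≥32, and no mortality gradient above 32 is given.
- **That the information gain must be 16–24%.** That follows only if mortality below GAHS 9 is taken as 10–20%, which implies about 37–50% of patients at ≥9. The article gives neither figure. At shares of 20–30% the gain is about 6–11%.
- **That the 60% figure certainly applies within this population.** The Background does not say that it was measured among patients with DF ≥32.

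**Conclusion.** The point holds as a nearly free improvement. The analysis as stated is valid, and both the 513 per margin and the planned power stand. Pre-specifying GAHS would add about 1–4 percentage points of power at 1,080 evaluable patients, equivalent to roughly 6–24% more information. The planned risk group may already carry some of the same prognostic content, so the true gain is probably somewhat lower. The simulation with a flag in both models suggests that most of it remains. The gain in points is larger if the drugs work less well than planned.

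These figures assume 60% mortality at GAHS ≥9 within the trial population, 20–50% of patients at or above that cut-off, a common odds ratio and no interaction. Beyond efficiency, the benefit is that the adjusted model is fixed before the results are known.

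**What to change.** Pre-specify baseline GAHS as a continuous score, or its components, in the primary 28-day logistic model and in the 90-day, 12-month and Cox models. It should sit alongside region, risk group and both treatment indicators. Keep the strata-only model as a sensitivity analysis, and report a standardised risk difference beside the conditional odds ratio so that the result can be read against the 30% to 21% planning margin. If the statistical analysis plan already does this, only a check is needed.

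The cost is about one sentence, using a score the trial already plans to use. There are two small downsides: the odds ratio becomes conditional on GAHS, and a simple rule for missing baseline values is needed.

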## Discussion

An objective review of the literature on the treatment of alcoholic hepatitis inevitably encounters the controversy over the use of corticosteroids and the lack of confirmatory data on the use of pentoxifylline. Current international guidelines recommend the use of corticosteroids except in patients with sepsis, where pentoxifylline is the first choice of treatment [26]. These recommendations are attributed a lower grade of evidence acknowledging the controversies outlined above. Given the importance of this condition, a definitive large trial was required to settle the dilemma. If corticosteroids prove to be successful in this trial, it would still be reasonable to expect a mortality rate of 20% in treated patients based on the analysis of recent trials. There will remain an unmet medical need in this field, but at least future trials will legitimately use a steroid (or pentoxifylline) control arm based on solid evidence.

At the heart of the controversy over the use of corticosteroids is susceptibility to infection. Although 40 mg daily of prednisolone is considered a moderate dose, this group of patients is already highly susceptible to infection and corticosteroids are likely to exacerbate this problem. The emergence of infection during treatment is associated with a significant increment in the mortality rate [23].

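### For sepsis, GI bleeding and renal failure the plan states only a descriptive by-arm summary; the factorial comparisons are written for mortality alone

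*Protocol article*

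**What the plan says.** The Clinical study endpoints section lists among the secondary endpoints "rates of gastrointestinal haemorrhage and sepsis, and rates of new or recurrent renal failure".

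The Statistical analyses section defines the factorial contrast for the primary endpoint: "the 28-day mortality rate in those treated with prednisolone (that is, Groups B and D) will be compared" with Groups A and C, and pentoxifylline is handled likewise with C and D against A and B. It then extends the approach to later deaths: "Mortality rates at 90 days and 12 months will be compared using the same strategy". Overall mortality also gets Kaplan-Meier and Cox analyses. For the three complications the stated analysis is one sentence: "Rates of gastrointestinal bleeding, sepsis and renal failure will be summarised over time and by arm".

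A general sentence in the same section reads "All analyses will be adjusted for the stratification variables and assessed at the two-sided 5% significance level". It follows directly on the mortality text and names no contrast for the complications.

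On why these outcomes matter, the Background says that "detractors cite the risks of sepsis and gastrointestinal haemorrhage with corticosteroid therapy", and the Discussion says "At the heart of the controversy over the use of corticosteroids is susceptibility to infection".

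**The concern.** The article gives these endpoints a method, and it is a weaker one than mortality receives. A summary by arm names no treatment contrast, no effect measure and no interval. The power section uses the word arm for the four randomised groups, so the natural reading is four columns of about 300 patients each.

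At stake is the harm side of the benefit-risk judgement on prednisolone. If prednisolone lowers 28-day mortality, clinicians will want to know what it costs in infection. If it does not, they will want to know whether infection offset a benefit. The Discussion itself says that an earlier trial's treatment groups diverged after day 28 because of infection on steroids. A sepsis contrast chosen after unblinding would be open to dispute in a way that a prespecified one is not.

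**Working it through.** **1. The plan's own figure.** The inputs, from the Power calculation section, are 30% v 21%, two-sided 5%, 90% power and a continuity-corrected chi-square test.

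- Uncorrected: n' = [1.960 × √(2 × 0.255 × 0.745) + 1.282 × √(0.30 × 0.70 + 0.21 × 0.79)]² / 0.09² ≈ 490.8, so 491.
- Corrected: n = (n'/4) × [1 + √(1 + 4/(n' × 0.09))]² ≈ 512.8, so 513.

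This matches the stated 513 per margin and 1,026 in total. No stated figure is wrong.

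**2. Group sizes.** Equal allocation of 1,200 gives 1,200/4 = 300 per arm and 600 per margin.

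**3. Precision of a sepsis difference.** The document gives no sepsis rate, so the rates below are assumptions. Half-width = 1.96 × √[(p₁(1−p₁) + p₂(1−p₂))/n]. For 10% v 15% the numerator under the root is 0.09 + 0.1275 = 0.2175:

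- n = 600: 1.96 × √(0.2175/600) = 3.7 points
- n = 300: 1.96 × √(0.2175/300) = 5.3 points

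| Assumed risks | 600 v 600 | 300 v 300 |
|---|---|---|
| 10% v 15% | 3.7 | 5.3 |
| 15% v 20% | 4.3 | 6.1 |
| 20% v 27% | 4.8 | 6.8 |
| 20% v 30% | 4.9 | 6.9 |

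The ratio is √2 whatever the rates. With only the 1,026 patients of the power calculation (513 per margin, about 256 per arm), 10% v 15% gives 1.96 × √(0.2175/513) = 4.0 points against 1.96 × √(0.2175/256) = 5.7.

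For the 5-point difference at 10% v 15%, the marginal half-width is smaller than the difference and the single-pair half-width is larger.

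**4. Effect of differential death.** Suppose the hazard of sepsis is the same in both groups, hazards are constant, and death follows the planned 30% v 21%. With H_s = −ln(1 − net sepsis risk) and H_d = −ln(1 − mortality), the expected proportion with sepsis by day 28 is H_s/(H_s + H_d) × [1 − exp(−(H_s + H_d))].

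Worked at a net risk of 20% (H_s = 0.2231):

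- 30% mortality: 0.2231/0.5798 × (1 − 0.8 × 0.70) = 16.9%
- 21% mortality: 0.2231/0.4589 × (1 − 0.8 × 0.79) = 17.9%

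| Net sepsis risk | 30% mortality | 21% mortality | Difference (points) |
|---|---|---|---|
| 10% | 8.4% | 8.9% | 0.5 |
| 20% | 16.9% | 17.9% | 1.0 |
| 30% | 25.5% | 26.9% | 1.4 |

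The group with fewer deaths shows slightly more sepsis with no true effect on the sepsis hazard. The distortion is small beside the 5- to 10-point differences in step 3.

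**The case against.** The strongest reply is that this is a journal article. Effect measures and competing-risk methods for complications are commonly left to the full protocol or SAP, and nothing in the text forbids a marginal comparison. This stands for the handling of death, which is not a fault here. It does not dispose of the main point, because the article states a method for these endpoints and sets it beside explicit contrasts for mortality. The general sentence on adjustment and the 5% level is ambiguous in scope. Even read broadly, it supplies no contrast for the complications.

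Four stronger readings are tempting, and the documents do not support them:

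- **That the trial cannot settle the infection question.** The stated primary objective is mortality. The Discussion makes infection central to the dispute over corticosteroids, not the trial's own primary question, and points to 90-day mortality as the comparison that captures late divergence. Sepsis and bleeding are assessed repeatedly, and marginal rates can be recovered by adding arm counts.
- **That the plan has low power for sepsis.** At an assumed 10% v 15%, power is about 75% at the margins and 46% for one pair of arms. But no arm-against-arm test is planned, and a descriptive summary has no power, so 46% does not describe this plan.
- **That ignoring death could make an effective drug look clearly harmful.** Step 4 gives 0.5 to 1.4 points. With complete follow-up, a cumulative incidence that treats death as competing equals the crude proportion, so a risk difference on that scale would keep the artefact.
- **That renal failure is pentoxifylline's proposed mechanism.** The Background gives inhibition of tumour necrosis factor alpha as a partial mechanism. Fewer hepatorenal deaths was one trial's result.

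**Conclusion.** The point holds as a weakness in the stated analysis. For three named secondary endpoints the article commits to description by arm and reserves the factorial contrasts for mortality. It therefore prespecifies no estimate of either drug's effect on these complications, and its arm-level presentation is less precise by a factor of √2: about 5.3 points against 3.7 at an assumed 10% v 15%.

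The sizes rest on assumed sepsis rates, equal allocation, full recruitment and unadjusted binomial intervals. The death calculation also assumes constant hazards and a death hazard that sepsis does not alter. Reading a margin as the effect of a drug whether or not the other is given relies on the no-interaction assumption already used for mortality. No figure is wrong, no passages contradict each other, and neither the design nor the data collection stands in the way.

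**What to change.** Before unblinding, replace the summary sentence with a prespecified analysis of sepsis, GI bleeding and renal failure, each as the proportion with at least one event by day 28 and by day 90:

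- Compare B+D with A+C and C+D with A+B, giving a risk difference or odds ratio with a 95% confidence interval, adjusted for region and risk group.
- Keep the four-arm table as description. It also shows whether the two drugs together behave differently from either alone.
- Report deaths without the event beside each proportion, so that differential survival is visible.
- A cause-specific hazard ratio is optional where onset dates exist. The article shows ascertainment over intervals, with a telephone interview at day 28 for patients discharged early, so dates should not be taken for granted.

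No extra patients or visits are needed. The cost is a few more secondary estimates, to be labelled as not multiplicity-controlled.
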